### Defining success

Pilot success will be graded using a traffic light system. The pilot will be deemed a success and progression to phase III trial will be considered appropriate if the following criteria are met:Green (go):Recruitment rate of ≥ 75% of target (*n* = 9) achieved within the 12-month recruitment period.≥ 75% of patients commenced KD prior to chemoradiotherapy.Retention rate of ≥ 75% at 3 months.Diet acceptable to ≥ 75% of patients at 3 months.≥ 75% of the proposed data collection completed for each end point.
Amber (review):Recruitment rate of ≥ 50% of target (*n* = 6) achieved within the 12-month recruitment period.≥ 50% of patients commenced KD prior to chemoradiotherapy.Retention rate of ≥ 50% at 3 months.Diet acceptable to ≥ 50% of patients at 3 months.≥ 50% of the proposed data collection completed for each end point.
Red (stop):Recruitment rate < 50% of target (*n* = 5) achieved within the 12-month recruitment period.< 50% of patients commenced KD prior to chemoradiotherapy.Retention rate of < 50% at 3 months.Diet acceptable to < 50% of patients at 3 months.< 75% of the proposed data collection completed for each end point.

Retention rate, dietary acceptance and data collection will be assessed for each diet independently. Recruitment rate and dietary commencement will be assessed using data combined from both arms.

Any components of the pilot considered not feasible or unacceptable to patients will be evaluated prior to progression onto phase III clinical trial is considered. The Shanyinde, Pickering, and Weatherall [34] method will be used to categorise and assess the extent of the issue and the Bugge et al. [35] method will be used to evidence the decision-making process.

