### Intervention design

All participants will be invited to attend clinical consultations pre-diet, on initiating diet, 6 weeks from initiation, 12 weeks from initiation (primary completion) and every 3 months for a total of 12 months (secondary completion) or until dietary discontinuation if prior to this. Telephone consultations will take place post initiation at weeks 1, 3 and 9 to enable dietary ‘fine tuning’ (Table 1 and Fig. 1). All consultations will be undertaken with the same research dietitian. It is not possible to blind the participants or the investigators due to differences between the diets and dietary education required.

**Table 1 Tab1:** Study schedule

	Study period										
		Enrolment/diet allocation	Post allocation (on diet)								Close out
Timeline		1 week post-histology	1 week after clinic 1	1 weeks after clinic 2	3 weeks after clinic 2	6 weeks after clinic 2	9 weeks after clinic 2	12 weeks after clinic 2	6 months after clinic 2	9 months after clinic 2	12 months after clinic 2
Visit window	Post-histology	± 5 days	± 5 days before radiotherapy	± 3 days	± 3 days	± 5 days	± 3 days	± 5 days	± 10 days	± 10 days	± 10 days
Clinic visit	Telephone discussion	Clinic appointment 1 Consent, register, baseline assessment, randomisation	Clinic appointment 2 Commence diet	Telephone review 1	Telephone review 2	Clinic appointment 3 Diet review	Telephone review 3	Clinic appointment 4 Diet review	Clinic appointment 5 Diet review	Clinic appointment 6 Diet review	Clinic appointment 7 Diet review End of trial
Information sheet	X										
Informed consent		X									
Eligibility screen		X									
Randomisation		X									
Medical history review		X									
Medications review		X									
Anthropometry		X				X		X	X	X	X
Biochemistry		X						X	X	X	X
Food diary		X				X		X	X	X	X
Ketone diary						X		X	X	X	X
Quality of life (QoL) questionnaire EORCT QLQ C30		X				X		X	X	X	X
QoL questionnaire QLQ BN20		X				X		X	X	X	X
Food Acceptability Questionnaire		X				X		X	X	X	X
Dietary review		X	X	X	X	X	X	X	X	X	X
Ketone review				X	X	X	X	X	X	X	X

X = procedure carried out

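### For data collection, Red (below 75%) overlaps Amber (50% and above), so completeness from 50% to just under 75% is graded both stop and review

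*Protocol article*

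**What the plan says.** The Defining success section of the protocol article grades the pilot Green (go), Amber (review) or Red (stop) on five criteria. For data collection the three lines are:

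- Green: "≥ 75% of the proposed data collection completed for each end point"
- Amber: "≥ 50% of the proposed data collection completed for each end point"
- Red: "< 75% of the proposed data collection completed for each end point"

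The Red lines for the other four criteria are "Recruitment rate < 50% of target", "< 50% of patients commenced KD prior to chemoradiotherapy", "Retention rate of < 50% at 3 months" and "Diet acceptable to < 50% of patients at 3 months".

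The same section states that data collection, like retention and acceptability, is graded for each diet separately. It adds that components found infeasible will be evaluated, by two cited methods, before progression is considered.

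**The concern.** A traffic-light rule should give one colour for one result. Here the Red cut-off for data collection equals the Green cut-off, yet an Amber line is still printed between them. The same completeness figure can therefore be reported as a reason to stop or as a reason to review.

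The Rationale section says the pilot is meant to identify the diet to carry into a definitive trial, and this criterion is applied diet by diet. The Intervention design section says neither participants nor investigators can be blinded. If the conflict is still open when the data are graded, the choice between the two colours could be made by people who already know which diet it favours. Fixing progression criteria in advance is meant to prevent that.

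**Working it through.** The cut-offs are stipulated rather than calculated, so there is no figure of the plan's to reproduce. The check is to apply the printed lines to every possible completeness value.

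**Inputs** (all from Defining success). Let *c* be completeness for one end point in one diet arm. Green: *c* ≥ 75%. Amber: *c* ≥ 50%, read as 50% to < 75% because higher values are Green. Red: *c* < 75%.

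**Rules as printed**

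| Completeness | Green | Amber | Red |
|---|---|---|---|
| below 50% | no | no | yes |
| 50% to < 75% | no | yes | yes |
| 75% and above | yes | no | no |

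The overlap is the whole interval from 50% to < 75%, which is 75 − 50 = 25 percentage points wide. It is also the entire Amber range, so Amber never applies alone.

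**Rules with Red at < 50%, as in the other four criteria.** Below 50% is Red, 50% to < 75% is Amber, and 75% and above is Green. Each value has one colour, with no overlap and no gap.

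**What this means per arm.** Twelve patients allocated 1:1 give about 6 per arm. With one form per patient:

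- 2/6 = 33.3%: Red
- 3/6 = 50.0%: Amber and Red
- 4/6 = 66.7%: Amber and Red
- 5/6 = 83.3%: Green

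**How often the band could be reached (illustration only).** Assume that completeness for an end point equals 12-week retention, that retention is 70% as in the Sample size section, that there are exactly 6 patients per arm, and that patients are independent. Then the number completed is Binomial(6, 0.7):

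- P(3) = 20 × 0.7³ × 0.3³ = 20 × 0.343 × 0.027 = 0.185
- P(4) = 15 × 0.7⁴ × 0.3² = 15 × 0.2401 × 0.09 = 0.324
- P(3 or 4) = 0.185 + 0.324 = 0.509, about 51% per arm
- P(5 or 6) = 6 × 0.7⁵ × 0.3 + 0.7⁶ = 0.303 + 0.118 = 0.420, about 42% per arm (Green)

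For two independent arms, the chance that at least one falls in the band is 1 − (1 − 0.509)² = 1 − 0.241 = 0.759, about 76%.

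**The case against.** The overlap itself is hard to dispute. The case on the other side is that it matters little. It touches one of five criteria in a 12-patient pilot that is analysed descriptively. Meeting the criteria leads to progression being considered, not to an automatic decision. Infeasible components are to be evaluated by named methods first, and the Analysis plan section promises a detailed plan before the final analysis, which could settle the grade. A reader might also take the colours from the top down and stop at the first that fits, which would make 60% Amber. These points limit the consequence, and it is not established that the choice would be made after the results are seen. They do not remove the conflict: the article states no reading order, and taking Red first gives the opposite answer. The follow-up evaluation does not say which colour applies.

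Three stronger readings are tempting, and the article does not support them.

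- **That the expected result lies in the band.** Visits run "or until dietary discontinuation if prior to this", so one might infer that week-12 forms cannot exceed 70% of those randomised. But 70% is an expected rate, not a ceiling. With 6 per arm, 5 or more still has about a 42% chance on that same assumption. The Secondary outcome measures section also has quality-of-life and food-acceptability forms completed when the diet is stopped early. The article does not say whether assessments after discontinuation count in the denominator.
- **That some results have no colour.** One end point at 40% with the rest at 90% would be uncoloured only if Red needs every end point to be below the line. The wording can equally mean grading each end point on its own, and then nothing is left out.
- **That a new completeness denominator is needed.** That would redesign the criterion and goes beyond the error shown.

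**Conclusion.** The point stands as an internal inconsistency in the progression rule. For data collection, every completeness value from 50% to just under 75% is both review and stop, and Amber has no range of its own. This follows from the printed lines alone and needs no assumption about dropout or denominators.

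The match among the other four criteria makes a slip for below 50% the likelier explanation. A deliberately stricter stop line cannot be excluded, and in that case the Amber line is void. The figure of about 51% per arm shows that the band is not remote, but it holds only if completeness tracks 12-week retention at 70% with 6 patients per arm. It is not a forecast.

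**What to change.** Before any completeness figure is graded, change the Red line for data collection to below 50%, in line with the other four criteria. If a stricter stop line was intended, delete the Amber line for this criterion instead, so that 75% and above is Green and anything lower is Red. Either choice gives each value exactly one colour.

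In the same edit, state whether the colour is given to each end point separately or set by the worst end point.

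The cost is a correction to one line plus a clarifying sentence. No new data, visits or patients are needed.

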### Statistical considerations

#### Sample size

Feasibility data demonstrates a likely retention rate of 70% participants at 12 weeks. With a sample size of 12, we will be able to estimate retention rates of 70% to within a 95% confidence interval of ± 25.93% (Hooper [36]). Billingham et al. [37] demonstrate a median sample size of 30 (range 8–114 participants) for UK pilot studies, whilst Hertzog [38] reports on the statistical adequacy for sample sizes of 10–40, thus further justifying a sample size of 12 for the current trial.

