## Methods

### Aims and objectives

The aim of this trial is to investigate protocol feasibility and patient impact by comparing two KDs in an NHS setting, with a view to informing the design of future phase III clinical trials. The primary objective is to estimate retention rates to inform sample size calculations of future, definitive trials. Secondary objectives in relation to protocol feasibility include estimations of recruitment, enrolment and long-term retention rates and to obtain data on dietary compliance, dietary adjustments required to achieve ketosis, ketone and glucose levels, intervention time, protocol refinements and completeness of data. Secondary objectives related to patient impact include collating data on quality of life, food acceptability, gastrointestinal side effects, biochemical markers and anthropometry.

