### Sample size and recruitment

This study is being conducted as part of a PhD thesis. Twelve patients will be recruited over a 12 months period. Previous feasibility work shows this recruitment rate is achievable. Patients will be identified at a weekly neuro-oncology multi-disciplinary team (MDT) meeting; with documentation within MDT case sheet deemed an appropriate referral. Patients will be approached for recruitment after surgery and histological diagnosis of GB. Recruitment will take place for 12 months from the date of opening. Patients referred for the KEATING trial will be offered a screening appointment. A screening log will be maintained for all patients referred to the trial and reasons for ineligibility will be noted.

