### Allocation strategy

Patients will be randomised into MKD or MCT KD groups. The patients will be informed of diet group by telephone. A permuted block randomisation method will be adopted, at a 1:1 ratio using ‘sealedenvelope’™ randomisation system. This will be set up and administered by the statistician ([name]) who is not involved with the recruiting of patients.

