### Primary outcome measures

Assess retention and drop-out rates defined as:The number of patients who start randomised treatment as a proportion of the number randomised, with reasons for non-compliance.The number of patients who complete 12 weeks of diet as a proportion of the number randomised, with reasons for non-compliance.The time to dietary discontinuation (week 12 or duration to discontinuation if prior to this).A description of barriers and facilitators to data collection and participant retention will also be included.

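### The ±25.93-point precision for retention applies to both diets pooled (n = 12), but retention is graded diet by diet on about 6 patients, where the same formula gives ±36.7 points

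*Protocol article*

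**What the plan says.** All references are to the protocol article.

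- **Aims and objectives:** "The primary objective is to estimate retention rates to inform sample size calculations of future, definitive trials". It does not say whether the rate is pooled or per diet.
- **Primary outcome measures:** 12-week retention is defined as "The number of patients who complete 12 weeks of diet as a proportion of the number randomised". Again no level is named.
- **Sample size:** the planning value is given as "Feasibility data demonstrates a likely retention rate of 70% participants at 12 weeks", and the justification is that with 12 patients "we will be able to estimate retention rates of 70% to within a 95% confidence interval of ± 25.93" percentage points. No other precision figure appears.
- **Sample size and recruitment, Allocation strategy:** "Twelve patients will be recruited over a 12 months period", and "A permuted block randomisation method will be adopted, at a 1:1 ratio". Twelve is therefore the total over both diets.
- **Defining success:** retention at 3 months is graded Green at 75% or more, Amber at 50% or more and Red below 50%. The level is explicit: "Retention rate, dietary acceptance and data collection will be assessed for each diet independently". Pooling is kept for two other criteria: "Recruitment rate and dietary commencement will be assessed using data combined from both arms".

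**The concern.** The precision statement and the decision rule refer to different quantities. The half-width is for one proportion among 12 patients. The retention grade is given twice, once per diet, each time on about half that number. A reader of the Sample size section would take ±25.93 points as the precision of the retention result that drives progression, because nothing there says that it applies only to the pooled rate.

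Retention is the primary outcome, and the stated purpose of comparing the diets (Rationale, Conclusion) is to find which one is more deliverable and better adhered to. The per-diet rate is therefore the one that readers will act on, and its precision is not stated anywhere.

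**Working it through.** **Inputs.** Planning retention p = 0.70, total n = 12 and 95% confidence (Sample size); 1:1 allocation (Allocation strategy), so 12/2 = 6 per diet. The article does not print 6 per diet; it is derived.

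**1. Reproduce the stated figure.** Normal-approximation half-width = 1.96 × √(p(1 − p)/n).

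- n = 12: 1.96 × √(0.21/12) = 0.2593, or ±25.93 points (44.1% to 95.9%).

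This matches exactly, so the figure is the normal approximation for all 12 patients.

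**2. Same formula at the level of the retention grade.**

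- n = 6: 1.96 × √(0.21/6) = 0.3667, or ±36.7 points (33.3% to 106.7%).

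Halving n multiplies the half-width by √2: 25.93 × 1.414 = 36.67. The upper limit passes 100%, so a symmetric ± is a poor description at this size.

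**3. Wilson interval at 70%.** Centre = (p + z²/2n)/(1 + z²/n); half-width = z√(p(1 − p)/n + z²/4n²)/(1 + z²/n), with z = 1.96.

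- n = 6: centre (0.70 + 0.320)/1.640 = 0.622; half-width 1.96 × √(0.0350 + 0.0267)/1.640 = 0.297. Limits 32.5% to 91.9%.
- n = 12: limits 42.1% to 88.2%.

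The n = 6 interval contains both 50% and 75%.

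**4. Attainable results in an arm of 6.** Green needs at least 0.75 × 6 = 4.5, so 5 of 6. Red is below 0.50 × 6 = 3, so 2 or fewer. Exact (Clopper-Pearson) 95% intervals:

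| Retained | Grade | Exact 95% interval |
|---|---|---|
| 4/6 | Amber | 22.3% to 95.7% |
| 5/6 | Green | 35.9% to 99.6% |
| 6/6 | Green | 54.1% to 100% |

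**5. What this does to the grade.** Binomial probabilities for one diet with n = 6:

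- True retention 70%: P(Green) = 0.42, P(Red) = 0.07, so P(Amber) = 1 − 0.42 − 0.07 = 0.51.
- Two diets both truly at 70% get different colours with probability 1 − (0.42² + 0.51² + 0.07²) ≈ 0.56.
- True retention 50%: P(Green) = 0.11.

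**6. Smaller recruitment.** Nine patients still meets the Green recruitment criterion and leaves 4 or 5 per diet: 1.96 × √(0.21/5) = 0.402 and 1.96 × √(0.21/4) = 0.449, or ±40 to ±45 points.

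**The case against.** The best defence is that nothing in the Sample size section is miscalculated. It says openly that the figure is for 12 patients, the primary objective and outcome do not specify per-diet estimation, and for a pooled rate ±25.93 points is right. The Practical considerations section also concedes some statistical uncertainty with 12 patients and promises caution. The cut-offs apply to the observed rate, not to a confidence limit, and infeasible components are to be evaluated by structured methods before progression is considered.

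Much of this stands. A reader might infer an arithmetic error; there is none. The general caution is real, but it mentions neither 6 patients per diet nor the effect on the retention grade, so it does not repair the mismatch.

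Three further inferences go beyond the documents:

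- *That no per-diet result can separate Green from Red.* An arm at 6/6 has an exact lower limit of 54.1%, above the Red boundary, and an arm at 0/6 has an exact upper limit of 45.9%. Nor is the difficulty confined to small arms: 9/12 pooled, exactly 75%, has an exact interval of 42.8% to 94.5%. Splitting by diet makes the imprecision larger; it does not create it.
- *That the final analysis will use an unsuitable interval.* The Analysis plan section promises descriptive statistics for retention and defers detail to a later plan. The normal approximation appears only as a planning half-width, and the choice of interval may properly be left to that plan.
- *That pooled retention should be carried forward because it is more precise.* The Rationale takes only the successful diet into the definitive trial, so a rate averaged over two diets would describe neither.

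**Conclusion.** The point holds as a mismatch between the precision statement and the unit of decision. The only precision figure supporting the sample size is right for the pooled rate and wrong as a description of the rate that is graded. At the article's own planning value the half-width per diet is ±36.7 points instead of ±25.93, about 41% wider (36.67/25.93 = 1.41), and the Wilson range of about 33% to 92% spans both cut-offs.

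This assumes that all 12 patients are recruited, that allocation ends at 6 and 6 (block size is not stated, so a small imbalance is possible), that true retention is near 70% in each diet, and that retention at 3 months in Defining success is the 12-week retention of the Sample size section. With fewer patients the per-diet precision is worse. The planned descriptive analysis remains valid; what needs correcting is what the reader is told about its precision.

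**What to change.** Replace the precision sentence in the Sample size section with wording such as: *Pooled over both diets (n = 12), 70% retention is estimated to about ±26 percentage points; per diet (n = 6), the unit used for the progression decision, to about ±37 percentage points (Wilson 95% interval about 33% to 92%).*

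In Defining success, or in the analysis plan still to be written, add that each diet's retention will be shown with a Wilson or exact 95% interval beside its traffic-light grade. The cut-offs and the per-diet rule can stay as they are.

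The cost is a few lines of text and a less favourable stated precision. No extra patients, visits or tests are needed.

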#### Analysis plan

A detailed analysis plan will be developed prior to the final analysis. In brief, descriptive statistics will be used to summarise retention, recruitment rates, enrolment adherence, dietary adjustments, dietetic time, dietary compliance, MCT supplement compliance, ketosis, anthropometry changes, biochemistry changes, quality of life, food acceptability and gastrointestinal side effects. The Kaplan-Meier survival curve will be estimated for overall survival and progression-free survival and displayed graphically with 95% confidence intervals.

## Discussion

### Practical considerations

When designing the trial, we considered a number of practical issues to enable implementation within an NHS setting.

When deciding on which KDs to include within the trial, nutritional adequacy and previous evidence base were considered. There are various types of KDs, offering varying contents of fat and carbohydrate. From the literature the two KDs previous cited in oncology case series include the MKD and the MCT KD [13, 14, 39, 40]. Both diets allow for the sufficient provision of protein, essential for patients undergoing oncological treatments, in comparison to the classic ketogenic diet which would not meet adult protein requirements. Both MCT and MKD are currently used in NHS practice for patients with refractory epilepsy.

In this trial, the KD will be offered alongside current standard of care. In order to allow for future meta-analysis of data, the diet will be commenced post-surgical resection, prior to chemoradiotherapy in keeping with US centres [41, 42]. This theory is supported by previous animal models which illustrate the KD to enhance the effects of chemoradiation [6–8].

Methods for assessing ketone and glucose levels were also considered. Blood ketone and glucose levels can provide a more accurate result, when compared to urinary ketones, due to the effects of urinary dilution. However, blood monitoring is more invasive for the patient and considerably more expensive when considering trial design and potential future NHS implementation. The minimum ketone monitoring requirements cited by the International League Against Epilepsy Task Force for Diet Therapy state urinary ketones to be a minimum standard [43]. Therefore, in keeping with this, we will conduct urinary ketone monitoring, with additional weekly blood ketone and glucose levels (home finger prick testing), with a view to informing future methodology.

In terms of recruitment, 12 patients is an achievable target and suitable for a pilot study, however, an element of statistical uncertainty will be present. Therefore, we have opted for descriptive statistical methods and will apply caution when interpreting results for any future study design.

